## Abstract

**Background:**

There is concern about the lack of diversity in children’s diets, particularly low intakes of fruit and vegetables and high intakes of unhealthy processed food. This may be a factor in the rising prevalence of obesity. A reason for the lack of diversity in children’s diets may be food neophobia. This study aimed to promote a healthy and varied diet among toddlers in kindergarten. The primary objectives were to reduce food neophobia in toddlers, and promote healthy feeding practices among kindergarten staff and parents. Secondary objectives were to increase food variety in toddlers’ diets and reduce future overweight and obesity in these children.

**Methods:**

This is an ongoing, cluster randomized trial. The intervention finished in 2014, but follow-up data collection is not yet complete. Eighteen randomly selected kindergartens located in two counties in Norway with enrolled children born in 2012 participated in the intervention. The kindergartens were matched into pairs based on background information, and randomly assigned to the intervention or control groups.

A 9-week multi-component intervention was implemented, with four main elements: 1) kindergarten staff implemented a pedagogical tool (Sapere method) in daily sessions to promote willingness to try new food; 2) kindergarten staff prepared and served the toddlers a cooked lunch from a menu corresponding to the pedagogical sessions; 3) kindergarten staff were encouraged to follow 10 meal principles on modeling, responsive feeding, repeated exposure, and enjoyable meals; and 4) parents were encouraged to read information and apply relevant feeding practices at home. The control group continued their usual practices. Preference taste tests were conducted to evaluate behavioral food neophobia, and children’s height and weight were measured. Parents and staff completed questionnaires before and after the intervention. Data have not yet been analyzed.

**Discussion:**

This study provides new knowledge about whether or not a Sapere-sensory education and healthy meal intervention targeting children, kindergarten staff, and parents will: reduce levels of food neophobia in toddlers; improve parental and kindergarten feeding practices; improve children’s dietary variety; and reduce childhood overweight and obesity.

**Trial registration:**

ISRCTN74823448 DOI 10.1186/ISRCTN74823448

## Background

A healthy diet is important for children’s development and growth during infancy and toddlerhood [1]. A healthy diet is also important for future health and morbidity, especially for non-communicable diseases such as diabetes, coronary heart diseases, and cancer [2]. There is concern about the composition of and lack of diversity in some children’s diets [3]. Some researchers suggest that a lack of diversity with a corresponding low intake of fruit and vegetables and high intake of unhealthy processed food, is caused by reluctance to try new food [4], and may be a contributing factor to the rising prevalence of obesity [3, 5, 6].

Taste preferences and food habits develop during infancy [7]. When solid food is introduced, the child is exposed to a diversity of foods and drinks, which may be the foundation for healthy and diverse eating habits [3]. Eating a variety of foods is essential to achieve adequate macro- and micronutrient intakes, and those with more varied food choices have better dietary quality [8]. Food neophobia, generally defined as reluctance to eat or avoidance of new foods, has become a central concept in discussions of diet and diversity, with food reluctance affecting both the quality of what children eat and what is served [3]. Food neophobia increases from around the age of 2 years, and decreases later in childhood [3]. An Australian study with 2- to 5-year-old preschoolers found that food neophobia was associated with lower intake of specific foods, such as vegetables [4]. They also found food neophobia was associated with children liking fewer types of food, having less variation in their food preferences, having a higher number of untested foods, and less healthy food preferences in general [4]. An American study aiming to increase preschoolers’ willingness to try new foods found that children started to like new food when they were exposed several times, and were given opportunity to explore, experience, and eat new food in a positive learning environment [9].

There are no studies in Norway that have specifically evaluated the lack of diversity in toddlers’ diets, or levels of food neophobia. Results from national dietary surveys of children aged 12 and 24 months showed that their diets were mostly consistent with current guidelines [10, 11]. However, about 17 % still ate “baby food” at age 24 months, and generally had a low intake of vegetables and high intake of processed food. Correspondingly, there is a high prevalence of overweight among infants and toddlers [12]. The most recent estimates from Norway show that 11–16 % of Norwegian children are overweight or obese before they reach the age of 6 years [12]. A possible way to reduce food neophobia and increase dietary diversity may be to increase levels of home cooking (and reduce processed food), thereby increasing the number and variety of foods presented to children [13]. This may potentially reduce the number of overweight children [6]. In a study conducted in the United Kingdom, vegetable consumption increased when 2- to 5-year-olds ate home cooked food [14]. However, there are no available studies focused on home cooked food.

Parents and other caregivers are central to a child’s food intake and meal patterns [15]. They decide what kind of food is bought and served, and are also involved through their food parenting style. Birch and colleagues argued that to provide guidance on responsive feeding, recognizing hunger and fullness and setting limits are important in interventions to improve children’s diets and prevent obesity [15]. There are several studies showing associations between parental food-related behaviors, feeding practices or food parenting, and children’s weight status [16]. However, most studies are cross sectional, and few have explored whether or not they can change parents/caregivers feeding practices [16].

Toddlers in Norway spend much of their time in kindergarten [17]; food and feeding practices in kindergartens influence children’s diet and eating habits, which in turn affects public health [18]. Mikkelsen et al. recently reviewed healthy eating interventions in preschools and concluded there was a scarcity of properly designed healthy eating interventions that used clear indicators and verifiable outcomes [19]. A national survey of meals in Norwegian kindergartens found that one of the most important challenges is the low number of kindergartens offering vegetables, with only 36 % serving vegetables every day [20]. This highlights a need for dietary interventions in kindergartens. The survey asked kindergarten staff what they thought were the most important factors for healthy food and meals in kindergarten; 49 % said staff attitudes were important, while 47 % thought that more courses were important [20]. This highlights the need for dietary interventions in kindergartens that include staff training and provision of pedagogical tools.

A possible solution is to educate kindergarten staff about the Sapere method, based on Puisais’ work [21]. This is a way of learning about food through senses (sight, touch, smell, taste, hearing) and language in kindergartens and schools. It aims to promote the building of healthy, balanced eating habits which help to prevent overweight [21]. At ages 2–3 years, children start to categorize and reason about foods [22]. Sensory lessons and meals based on the Sapere method aim to give children food experiences that help them recognize, differentiate, categorize, and reason about foods, and arouse curiosity about new foods [21]. Although the Sapere method is used in several European countries, there is limited research on its effect on child health [23]. In Norway, there is a lack of methods for use in kindergartens to introduce children to varied and balanced diets. To our knowledge, the Sapere method has not previously been tested in Norway; therefore, we used this method in the present intervention.

### Objectives and outcomes

The present study aimed to provide new knowledge about promoting a healthy and varied diet in toddlers by reducing levels of food neophobia. The intervention may also help to prevent future overweight. The intervention was multi-component intervention and used social ecological thinking, and included individual-level predictors as well as social and physical environmental determinants. The intervention was based on theories of healthy eating habits and food neophobia.

Our specific research question was: Can an intervention involving Sapere-sensory education and healthy meal preparation targeting children, kindergarten staff, and parents reduce levels of food neophobia in children, improve parental and kindergarten staff feeding practices, improve the variety and healthiness of children’s diets, and reduce future child obesity?

#### Primary outcomes

Children’s levels of food neophobia; assessed at baseline, after the intervention, and when the child reaches the age of 4 years.Parental and kindergarten staff feeding practices; assessed at baseline and after the intervention, and parental feeding practices assessed when the child reaches 4 years.

#### Secondary outcomes

3.Child dietary habits and food variety; assessed at baseline, after the intervention, and when the child reaches 4 years.4.Child body mass index and weight; assessed before and after the intervention, and when the child reaches 4 years.

#### Other study outcomes

Other study outcomes are: parental food intake, food variety, level of food neophobia, self-reported weight and height; and the level of food neophobia in kindergarten staff along with their self-reported cooking skills, knowledge, and attitudes relating to food.

## Methods

### Study design

This study used a cluster randomized controlled design to test a multi-component kindergarten-based intervention to improve dietary habits in toddlers. The study started in 2014 with follow-up studies planned for 2016 and 2017.

In total, 18 kindergartens participated in the study, with the director of each kindergarten consenting to participate on behalf of the kindergarten. Norwegian kindergartens are organized in different ways, but are usually divided into different departments. Two of the participating kindergartens had two departments for toddlers (aged 0–3 years), giving a total of 20 participating departments. These departments were randomized to either the control or intervention group.

The pedagogical leaders in the participating departments distributed a short invitation letter in both paper and electronic versions (an email link) to the parents, and a paper version to kindergarten staff. More detailed information about the study was provided on the study’s web page, and parents and kindergarten staff provided consent to participate via the web page.

The children’s parents completed a questionnaire covering food neophobia, parental feeding practices, food variety, and background variables at baseline and just after the intervention. Parents in the intervention group also answered evaluation questions after the intervention. Preference taste tests were conducted to assess the children’s behavioral food neophobia at baseline and after the intervention. Further follow-up is planned when the children are aged 4 years, in which parents will complete a short questionnaire with key questions. The children’s weight and height were measured pre- and post-intervention, and will be collected from health cards at age 4 years.

Participating kindergarten staff completed questionnaires before and after the intervention about food neophobia, feeding practices, cooking skills, and food-related knowledge and attitudes. Staff in the intervention group also answered evaluation questions after the intervention. In addition, pedagogical leaders were asked to assess the implementation of the intervention.

The intervention occurred over a 3-month period. The intervention program ran 3 days per week for 9 weeks; with 3 weeks without intervention topics (see detailed description below). The control group continued with their usual practices.

The baseline study for this randomized control trial using child and parent data drew on a larger cross-sectional sub study entitled “Preschoolers’ food courage,” in which all kindergartens in the counties of Vest-Agder and Aust-Agder, Norway, were invited to participate. In total, 266 kindergartens participated and 510 parents completed questionnaires. For parents who participated in the present intervention but not in the cross-sectional study, and had therefore not completed the baseline questionnaire, the baseline questionnaire was completed before the intervention (*n =* 88).

### Study population

The primary study population was 2-year-olds. Inclusion criteria for children were: born in 2012, attended the included kindergartens in Vest-Agder and Aust-Agder, were in kindergarten departments for toddlers, and had a parent that understood Norwegian.

There were 183 children enrolled in the 18 kindergartens who met the inclusion criteria. Of these, 116 children participated (participation rate, 63 %). There were 69 children in the intervention group and 47 children in the control group.

Of the participating children, 104 participated in preference taste test 1 (baseline) and 101 in preference taste test 2 (after intervention). There were 90 parents who completed the baseline questionnaire and 87 who completed the second questionnaire.

There were 89 kindergarten staff (assistants and pedagogical leaders); 82 participated at baseline (participation rate, 92 %). In total, 43 kindergarten staff participated in the intervention group and 39 in the control group. In the post-intervention study, 78 completed the questionnaire. There were 18 directors in the participating kindergartens, all of whom completed a questionnaire collecting descriptive information about the kindergartens and food offered in that kindergarten.

### Sample size calculation

Sample size was originally calculated according to the secondary weight outcome. For this outcome we wanted to observe a difference of 1 kg in weight over time between the two groups. According to a national survey, the standard deviation (SD) of 2-year-olds’ weight is 1.6 [11], with a power of 80 % and significance level of 5 %; therefore, 41 children needed to be recruited for each group. Due to possible dropout over time, we increased this to 45 children in each group. At the start of the study, we did not have a relevant SD for our primary outcome (level of food neophobia) in this age group. Our previous cross sectional trial of 510 2-year-olds (not yet published) indicated that the SD for food neophobia was 9.4, and a mean score reduction in the level of food neophobia from 18.2 to 12.0 would be of public health value. Using a power of 80 % and significance level of 5 %, this suggested 37 participants were needed in each group. Therefore, we aimed to include 10 kindergartens each in the control and intervention groups, and recruit about 45 children for each group.

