### Randomization

Of the 266 kindergartens in the previous cross-sectional study, 144 had eight or more toddlers born in 2012 who were eligible for inclusion in the present cluster randomized trial. Of these, 50 kindergartens in the two Agder counties were randomly selected and invited to participate in the cluster randomized trial. After contacting the selected kindergartens, we realized that not all kindergartens had all enrolled 2012 children in one department. Therefore, we changed the kindergarten inclusion criterion from eight to a minimum of seven toddlers born in 2012 in one department. There were 42 kindergartens that satisfied this new inclusion criterion. Of these, 18 kindergartens agreed to participate and were matched into pairs. Kindergartens were matched according to urbanity, number of 2012-born children enrolled, and whether they had previously focused on nutrition. The pairs were then randomly allocated to the intervention or control group, with nine kindergartens (10 departments for toddlers) in each group. The kindergartens were informed about their group allocation after agreeing to participate. In the intervention group, one kindergarten withdrew from participation due to closing of the kindergarten, and one kindergarten in the control group had no parents of children who agreed to participate, leaving only the baseline results questionnaires from staff. In total, 16 kindergartens with 18 departments for toddlers participated in this study.

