## Discussion

There has been a call for intervention studies in preschools to promote healthy diet and weight development [19]. Recent studies have raised concern about the lack of variety in children’s diets, and have related this to the rise of overweight and obesity in preschool children [3]. With the study “Preschoolers’ food courage” we are investigating the effectiveness of a multi-component kindergarten-based intervention to: reduce food neophobia; increase food variety; increase healthy feeding practices in kindergarten and at home; and over time, reduce the prevalence of overweight in this group.

We developed an intervention that may be easily implemented in kindergartens. The intervention kit includes four elements: a pedagogical tool (Sapere method), menu of associated lunch dishes, 10 practical tips for healthy eating in children, and postcard messages for parents.

The strengths of our study are that it is being conducted in a natural setting, making it possible to reproduce in other kindergartens if it shows an effect. Further, the use of the Sapere method, which was developed for children, makes it relevant for the kindergarten setting. The Sapere method is widely used in some countries; however, few studies have evaluated its effect on children’s diet and health [21]. Methodological strengths include objective measurements of children’s willingness to try new foods, and children’s weight and height at baseline and after the intervention.

However, our study also has some limitations. Recruitment of kindergartens and parents was difficult, and although we included the desired number of children, we should have included more children to have full datasets for 37 children in each group, as suggested by the power calculations; especially as a somewhat higher number may be needed due to the clustering effects. In the preference taste tests, we found that not all children were present on the day we arrived, and although we returned to some kindergartens for baseline measures, it was difficult to test all participating children. Further, it may be difficult to track the children at age 4 years, when they change kindergarten departments at age 3 years. Another limitation is generalizability, as only children from the two southern counties in Norway were included.

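### The sample sizes of 41 and 37 per group at 80 % power are those for individually randomised children; nothing in them allows for the randomisation of kindergartens

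*Protocol article*

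**What the plan says.** All of this is in the protocol article.

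- **Sample size calculation, weight:** "we wanted to observe a difference of 1 kg in weight over time between the two groups", with the input that "the standard deviation (SD) of 2-year-olds’ weight is 1.6", 80 % power and 5 % significance; "therefore, 41 children needed to be recruited for each group". The number is then raised to 45, and the only reason given is dropout.
- **Sample size calculation, food neophobia:** SD 9.4 and a fall in the mean score from 18.2 to 12.0, at the same power and significance level; "this suggested 37 participants were needed in each group". The section closes with the recruitment aim: "we aimed to include 10 kindergartens each in the control and intervention groups", with about 45 children per group.
- **Randomization:** "The pairs were then randomly allocated to the intervention or control group, with nine kindergartens (10 departments for toddlers) in each group". One kindergarten in each group then dropped out of the child data: "In total, 16 kindergartens with 18 departments for toddlers participated in this study".
- **Multivariate analysis:** linear mixed models are planned, partly because of the clustering.
- **Discussion:** among the limitations, more children should have been included to secure complete data on 37 per group, "especially as a somewhat higher number may be needed due to the clustering effects".

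**The concern.** Children in one kindergarten share staff, meals and, in the intervention group, the delivery of the programme, so their outcomes are likely to be positively correlated. Each child then carries less information about the group difference than an independent child would. In addition, the comparison rests on about 20 clusters, not on 74 to 90 independent observations. A sample size that ignores both features overstates power.

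What is at stake is how the result is read. Food neophobia is a primary outcome. If no difference is found, a reader who takes the 80 % at face value will treat that as stronger evidence against a 6.2-point effect than the design may support. The Discussion warns of this in general terms but still uses 37 as the benchmark.

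**Working it through.** **Inputs from the article.** Weight: difference 1 kg, SD 1.6. Neophobia: difference 18.2 − 12.0 = 6.2, SD 9.4. Power 80 %, significance 5 % (taken as two-sided, which reproduces the figures; one-sided gives 32 and 29). Planned: 10 kindergartens and about 45 children per group, so m = 45/10 = 4.5. Realised: 69 v 47 children, 87 second parent questionnaires, and 16 kindergartens (9 − 1 = 8 per group).

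**Assumed, because the article does not give them.** ICC 0.02 / 0.05 / 0.10. For the realised case: the 87 questionnaires split as 69:47, and a coefficient of variation (CV) of cluster size of 0.4.

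**Step 1: reproduce the stated figures.** n per group = 2(1.960 + 0.842)² SD²/Δ², where 2(1.960 + 0.842)² ≈ 15.70.

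- Weight: 15.70 × 2.56/1 = 40.2, rounded up to 41 (t-test solution 41.2).
- Neophobia: 15.70 × 88.36/38.44 = 36.1, rounded up to 37 (t-test solution 37.1).

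Both agree with the article at a design effect of exactly 1.

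**Step 2: design effect.** DE = 1 + (m − 1) × ICC = 1 + 3.5 × ICC = 1.07 / 1.175 / 1.35. Multiplying the stated sizes by DE and rounding up gives 44 / 49 / 56 for weight and 40 / 44 / 50 for neophobia, before any allowance for dropout.

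**Step 3: power at the planned sizes.** SE = SD × √(2 DE/n). Power is Φ(Δ/SE − 1.96) by normal approximation, or comes from the noncentral t with 2 × 10 − 2 = 18 df. Example, weight at ICC 0.05: SE = 1.6 × √(2 × 1.175/41) = 0.383, Δ/SE = 2.61, Φ(0.65) = 74 %.

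| Power, % | ICC 0 | 0.02 | 0.05 | 0.10 |
|---|---|---|---|---|
| Weight, n = 41, normal | 80.8 | 78.1 | 74.2 | 68.3 |
| Neophobia, n = 37, normal | 81.0 | 78.3 | 74.4 | 68.5 |
| Weight, n = 41, t 18 df | 76.3 | 73.5 | 69.5 | 63.5 |
| Neophobia, n = 37, t 18 df | 76.5 | 73.7 | 69.7 | 63.7 |
| Weight, n = 45, t 18 df | 80.1 | 77.4 | 73.5 | 67.5 |
| Neophobia, n = 45, t 18 df | 84.1 | 81.6 | 77.9 | 72.1 |

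Two sources of loss can be separated. Having few clusters costs about 4 to 5 points even at ICC 0 (81 % to about 76 %). The ICC costs the rest.

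**Step 4: how far the margin to 45 would reach.** By normal approximation, with no child lost, 45 absorbs a design effect of 45/41 = 1.098 for weight, which is ICC 0.098/3.5 = 0.028. For neophobia it absorbs 45/37 = 1.216, which is ICC 0.216/3.5 = 0.062.

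**Step 5: the neophobia questionnaire as collected.** 87 × 69/116 ≈ 52 and 87 × 47/116 ≈ 35, so m ≈ 6.5 and 4.4 per kindergarten. With unequal cluster sizes, DE = 1 + ((1 + CV²)m − 1) × ICC, and df = 16 − 2 = 14. Example at ICC 0.05: DE = 1.327 and 1.204, SE = 9.4 × √(1.327/52 + 1.204/35) = 2.30. Baseline adjustment with pre-post correlation r = 0.5 (assumed) multiplies the variance by 1 − 0.25 = 0.75. The difference detectable at 80 % power is about (2.145 + 0.868) × SE.

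| ICC | SE | Power, unadjusted | Detectable difference | Power, r = 0.5 | Detectable difference, r = 0.5 |
|---|---|---|---|---|---|
| 0.02 | 2.16 | 76 % | 6.5 | 87 % | 5.6 |
| 0.05 | 2.30 | 71 % | 6.9 | 82 % | 6.0 |
| 0.10 | 2.52 | 63 % | 7.6 | 75 % | 6.6 |

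**The case against.** **The authors disclose it, and the analysis handles it.** The Discussion says that clustering may raise the required number and that complete data on 37 per group were not secured. The mixed model is chosen with clustering in mind. This stands as mitigation: a reader might infer that the planned analysis is invalid, and the article does not support that. The fault lies in the planning power, not in the test. But the disclosure carries no figure, and the 80 % in the sample size section is left unqualified.

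**The recruitment target was 45, not 37.** For neophobia, 45 retained children per group keep 82 % power at ICC 0.02 even on 18 df. This also stands, but the article assigns that margin to dropout, so it covers clustering only if nobody is lost.

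**The size of the loss rests on an assumed ICC, and baseline adjustment is left out.** Correct. At ICC 0.01 the normal approximation still gives about 79 to 80 % at the stated sizes. With r = 0.5, realised power exceeds 80 % at ICC 0.02 and 0.05. Pair matching may also recover some power. A reader might therefore conclude too much by saying that the trial is underpowered whatever is assumed. The defensible statement is that the calculation does not establish 80 %: it uses neither baseline adjustment nor matching, and the article gives no correlation with which to credit them.

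**Scope.** The realised figures cover the questionnaire only. The SD of 9.4 does not carry over to the taste test, which 101 children took after the intervention. The article also speaks of departments as randomised in one place and of matched kindergartens in another. The realised calculation counts 16 kindergartens; 18 departments would change m and the df somewhat.

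**The weight SD.** Because weight is followed to age 4, a reader might infer that the SD for 2-year-olds is too small and that weight power is lower still. The article does not support this. It gives no SD at age 4, and a difference over time may mean a difference in change, whose SD could be smaller. The direction is unknown, so the point is not made here.

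**Conclusion.** The point holds as a fault in a stated calculation. That 41 and 37 are individual-randomisation figures is certain, since both reproduce exactly with a design effect of 1. It follows for any positive ICC that they do not by themselves secure 80 % power under cluster randomisation.

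The size of the shortfall is conditional. Over the assumed ICC range it is roughly 2 to 12 points below the nominal 80 % by normal approximation, and 6 to 17 points on 18 df, where about 4 points arise from the small number of clusters alone. For the questionnaire as collected, the outcome runs from 63 % (ICC 0.10, unadjusted) to 87 % (ICC 0.02, r = 0.5), so whether 80 % is reached depends on quantities that the article does not state.

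This should be fixed, but it is not critical: recruitment is complete, the planned model accounts for clustering, and only the claim about power changes.

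**What to change.** Rewrite the sample size paragraph so that it:

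1. says that 41 and 37 assume independent children;
2. applies the design effect 1 + (m − 1) × ICC, extended for unequal cluster sizes, over a stated and justified ICC range;
3. uses the realised clusters, names the unit counted (kindergarten or department), and uses the analysable children per group for each outcome in place of the pro rata split assumed here;
4. uses a reference distribution suited to the number of clusters;
5. replaces the unqualified 80 % with the resulting power range, or with the difference detectable at 80 %;
6. states the pre-post correlation if baseline adjustment is credited.

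The Discussion limitation should then cite those figures and stop using 37 per group as its benchmark.

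The cost is one reworded paragraph and a matching sentence. Data collection, recruitment and the planned model are unaffected. The stated power will probably look less favourable, unless the credit for baseline adjustment can be justified.
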